##### CBT fidelity measurement

All CBT therapists will be provided audio recording devices and asked to audio-record their sessions. We will randomly select 1 study case from each clinician (assigned after their initial 2 training cases); a trained fidelity rater will listen to all 12 sessions of this case and rate fidelity using a standardized fidelity checklist developed for *Coping Cat* [180, 181]. These fidelity rating checklists will allow raters to record the delivery of treatment components during each session and calculation of percent fidelity to the treatment model for each CBT therapist and overall, across all therapists in the study. We will also include a measure of general therapy competence that has been used with *Coping Cat* and can help assess the quality of treatment delivery, including exposure practices [185].

With the *Coping Cat* fidelity checklist used to measure clinician adherence to *Coping Cat*, and required record-keeping for number of sessions completed, it will be possible to conduct analyses of the association between *Coping Cat* adherence and dose, on the one hand, and improvement on patient centered outcome measures of anxiety symptoms on the other. In addition, given the central role of exposure and tolerance of negative affect in the *Coping Cat* conceptual model, and following procedures used in the CAMS study [119], we will have therapists complete brief reports following each session in which they rate the child’s overall adherence with treatment procedures, mastery of the information/skill covered in the session, and they will provide 3 kinds of information related to exposures: (1) the number of exposures used in the session, (2) difficulty level of the exposures (based on the child’s ‘subjective units of distress’ ratings), (3) level of skill/mastery shown by the child during the exposures. This will permit us to develop an index of tolerance of exposure and exposure mastery shown by the child, on the one hand, and patient-centered outcomes (Table 2) on the other.

#### Long-term follow-up

Recruitment will occur over the first 2 years. The last patients recruited will complete the 24-month trial at 2.5 years after study initiation, leaving a minimum of 12 months follow-up duration for those recruited last. We will continue following patients recruited earlier to provide longer-term follow-up data. Assessments will occur quarterly and will be identical in content to those obtained during the 24-week trial. During follow-up, patients and their clinicians will be able to select whatever treatment they wish, and at whatever frequency and intensity deemed desirable; insufficient responders or those who relapse during the follow-up period may switch to another medication or psychosocial therapy at the treating clinician’s discretion. We will encourage clinicians and patients to continue with successful treatments begun during the trial, however. Booster CBT sessions will be provided as needed, as occurs in regular (good) clinical practice. These sessions will not be scheduled at regular intervals but will instead occur in response to patient need and according to the provider’s clinical judgement. All booster sessions will involve review of the youth's FEAR plan developed during the initial phase of treatment and will use this plan as a base to address residual or recurring issues, avoidance, and functional impairment. The number of booster sessions, other treatments delivered, and any changes (including discontinuations), will be tracked and recorded carefully for consideration in analyses.

#### Adverse events (AEs)

These will be elicited by a combination of structured questions and direct, open-ended inquiry of patients and parents in each treatment arm of the study using the Pediatric Side Effect Questionnaire (a modified version of the Antidepressant Side Effect Questionnaire) at weeks 6, 12, 18, and 24 of the study. Clinicians will be requested to complete this form at each clinical visit; the form will be placed in the clinic chart, which a coordinator will then extract and enter into the study’s REDCap database. We will use the FDA definition to define a serious or unexpected AE [186]; for each reported AE, we will document whether it meets regulatory criteria for a serious or unexpected AE, and the presumed relationship to study procedures. Federal guidelines and recommendations for reporting serious or unexpected AEs to site IRBs and study’s DSMB will be followed [186]. Height, weight, blood pressure, and pulse will be assessed at each in-person study visit, and we will request that parents measure all except blood pressure for each telehealth visit [177]. The development of suicidality during treatment is a possibility; participants will therefore be assessed at each study visit with the Columbia-Suicide Severity Rating Scale (C-SSRS) [104]. Patients will be withdrawn from the study if continued participation is deemed unjustified due to risk of self-harm, and each study site will take appropriate measures to ensure safety.

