Patient-Identified Treatment Needs	Youth Top Problems [90]	C	All	6	69–.88	3	B,12,24,Q
Well-Being	PROMIS Purpose & Meaning Short Form [91]	C,P	All	8	.90–.98	1	B,12,24,Q
Life Satisfaction	NIH Toolbox Life Satisfaction [92]	C,P	3–17	5	.86–.97	3	B,12,24,Q
Self-Efficacy	NIH Toolbox Self-Efficacy [93]	C,P	7–17	10	.90–.92	3	B,12,24,Q
Family Functioning	Family Assessment Device [94]	C,P	12+	12	.69–.84	5	B,12,24,Q
Social Functioning	NIH Toolbox Social Relations & Loneliness [92]	C	7–17	29	.95	10	B,12,24,Q
School Functioning	Grade point average	Report card	N/A	N/A	N/A	N/A	B,12,24,Q
	School attendance	Report card	N/A	N/A	N/A	N/A	B,12,24,Q
	Student Subjective Wellbeing Questionnaire	C	7–17	16	.92	4	B,12,24,Q
Sleep	Sleep Self Report [95]	C	7–12	26	.76	7	B,12,24,Q
	Children’s Sleep Habits Questionnaire [96]	P	4–10	23	.68–.78	7	B,12,24,Q
Emotion Regulation	Brief Version of the Difficulties in Emotion Regulation Scale (DERS-16) [97, 98]	C	11–17	16	.92	2	B,12,24,Q
Coping with Change	Anxiety Control Questionnaire for Children [99, 100]	C	8–18	10	.89	2	B,12,24,Q
Comorbid Psychiatric Symptoms	Child Behavior Checklist [101] Youth Self-Report [102]	C,P	6–17 11–17	83 112	.78–.97 .71–.95	12	B,12,24,Q
	Mood and Feelings Questionnaire [103]	C,P	All	13		5	B,12,24,Q
Side Effects	The Pediatric Side-Effect Checklist	C,P,Cl	All	24	.78	5	B,6,12,18,24,Q
Suicidal Ideation	Columbia-Suicide Severity Rating Scale [104]	C	All	6	.73–.93	2	B,12,24,Q
Family’s Accommodation of Patient’s Symptoms	Family Accommodation Scale-Anxiety [105]	P	All	13	.82–.90	3	B,12,24,Q
Treatment Expectations	Treatment Expectancies [106]	C,P,Cl	All	3	N/A	2	B,M
Service Use	Anxiety Disorders Interview Schedule For DSM-5 (ADIS), the supplemental service form (SSF) [107]	P	All	5	N/A	5	B,12,24,Q
Treatment Preferences	Treatment Acceptability and Preferences [108]	C,P	All	2	.88	5	B,12
Clinician Relatedness & Therapeutic Alliance	Outcome Rating Scale and Session Rating Scale [109]	C,P,Cl	All	8	.87–.96 & .88	1	B,M
Anxious Avoidance	Child Avoidance Measure [110]	C,P	8–18	8	.86–.91	3	B,M,Q
Parent Anxiety & Depression Symptoms	PHQ9 & GAD7 [111, 112]	P	All	16	0.83–0.92 ([111, 112])	3	B,12,24

C=Child-report; P=Parent-report; Cl = Clinician-report

B=Baseline; 6 = Week 6; 12 = Week 12; 18 = Week 18; 24 = Week 24; Q = Quarterly Follow-up; M = Monthly, every 4 weeks during the 24-week trial

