#### Administration of Fluoxetine

##### Training in fluoxetine administration

Prospective prescribers for the study will include child psychiatrists, developmental behavioral pediatricians, general pediatricians, and psychiatric nurse practitioners working in one of our study sites. They will undergo a 3-hour training for the study with two senior psychopharmacologists before being assigned any patients for treatment. Training will include an overview of study design, measures, inclusion and exclusion criteria, rationale for selection of fluoxetine as the study medication, and review of the pharmacology and drug interactions of fluoxetine, known side effects, assessment of side effects, reporting of adverse events, study dosing guidelines, remission criteria, and on-line training in the Columbia Suicide Severity Rating Scale.

Stage 1 Fluoxetine Dosing is flexible to maximize therapeutic effects while minimizing side effects, and based on literature for fluoxetine [174–176] and FDA regulatory approvals [177]. The study’s starting dose, and minimum permitted, is 10 mg/day; should that not be tolerated, the patient will be withdrawn from active treatment (but not from study follow-up). After 1 week at 10 mg/day, the dose will increase to 20 mg/day. After completion of week 4, 10 mg/day dose increases are permitted every other week as tolerated, up to a maximum daily dose of 80 mg/day. If the patient is not in remission and does not have dose-limiting side effects, written guidelines will encourage the prescribing physician to increase the dose of medication. If patients are on doses > 20 mg/day, the total daily dose can be prescribed either once daily or split into twice daily administrations. If dose-limiting side effects occur, dosages can be reduced by 10–20 mg/day. Patients can be prescribed a dose that previously was not adequately tolerated if: 1) at least 2 weeks have elapsed since the dose was reduced, and 2) the patient/parent agrees to re-try the higher dose.

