#### CBT stage 1 implementation

We will use the *Coping Cat* program as the behavioral intervention for this study. *Coping Cat* is an established evidence-based CBT treatment for pediatric anxiety [180–182] that has been studied rigorously for more than 25 years. The CBT strategies that form the core of *Coping Cat* have been subjected to years of extensive research through clinical trials [183, 184], have been shown to be highly efficacious in addressing symptoms of a range of anxiety disorders, and are widely available at low cost. It is delivered in individual therapy sessions with anxious children.

*Coping Cat* comprises 4 core functional components **(**Table 1**)**:
Building a Collaborative Working Alliance: recognizing and understanding the emotional and physical reactions to anxiety;Undergoing exposure without Avoidance: clarifying thoughts and feelings in anxiety-provoking situations;Developing Coping Efficacy: developing plans for effective coping (e.g., modify anxious self-talk into coping self-talk, or determine what coping actions might be effective);Engaging in Reward: evaluating performance and giving self-reinforcement.

The Coping Cat workbook is used for children aged 8 to 13 years, and the parallel C.A.T. Project workbook is used for ages 14 to 17. For both age groups, the sequence of sessions follows the same structure: Introduction, including psychoeducation and development of an individualized anxiety hierarchy; Skills Building, including relaxation training and coping skills; and Experiential Practice, including exposure and practice of coping skills, moving from the least to most anxiety-provoking situations from an individualized anxiety hierarchy. *Coping Cat* will be delivered over 12 weekly therapy sessions in Stage 1 of our SMART study with minimal modification to the original *Coping Cat* protocol.

*Coping Cat* therapists will be those who normally provide therapy in the study sites; these include licensed mental health professionals (e.g., psychologists, social workers) and trainees (e.g., psychology interns, fellows). All will undergo *Coping Cat* training and participate in ongoing consultation and fidelity measurement. To promote optimal representativeness and external validity, there will be no requirements for prior training; *Coping Cat* training has demonstrated effectiveness with clinicians ranging from graduate students [180, 181] to experienced psychotherapists [49], with strong treatment effects in each case.

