#### Durability of the 24-week intervention

This will be assessed using the repeatedly-measured outcomes collected quarterly for 12 months following end of the trial intervention, following the theoretical and simulation approaches and results provided by Lu et al. (2016) [198] and Li (2017) [199]. These data will be modeled using marginal means models with generalized estimating equations, with weighting and replication of observations based on stage 1 responder status, as recommended for SMART designs. Using this approach, the post-intervention linear slopes as well as end-of-study absolute values in trial outcomes will be compared among the adaptive treatment strategies (assessing group-by-time interaction terms); we will also consider possible non-linearities in post-intervention trajectories with addition of polynomial terms for time of assessment. Adverse events will be categorized using the MedDRA coding system and compared between treatment groups using exact methods for comparisons of proportions.

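### Adverse events come from a common fixed schedule and from visit-driven clinician forms, and the planned comparison of proportions does not say which counts; pooling the two can bias it

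*Protocol article*

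**What the plan says.** The section "Adverse events (AEs)" of the protocol article sets up two sources.

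- **Fixed schedule.** Events are elicited "of patients and parents in each treatment arm of the study using the Pediatric Side Effect Questionnaire", "at weeks 6, 12, 18, and 24 of the study". This is the same for every arm.
- **Visit-driven.** "Clinicians will be requested to complete this form at each clinical visit". The form goes into the clinic chart, and a coordinator extracts it into the study database.

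Table 2 has a row for "The Pediatric Side-Effect Checklist", which I take to be the same instrument. It names child, parent and clinician as reporters, at baseline, weeks 6, 12, 18 and 24, and quarterly. It has no per-visit entry for the clinician.

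The analysis is at the end of the section on durability of the 24-week intervention. Events are coded with MedDRA and "compared between treatment groups using exact methods for comparisons of proportions". The source of the events and the counting unit are not named, and nothing adjusts for the number of contacts.

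On contacts, Coping Cat "will be delivered over 12 weekly therapy sessions in Stage 1 of our SMART study", and the CBT stage 2 section continues it weekly for 12 more weeks in the optimised arm. No number of medication visits is given. The Stage 1 dosing text says only that there is a step after week 1 and that, after week 4, "10 mg/day dose increases are permitted every other week as tolerated". Children in combination attend for both treatments.

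**The concern.** The proportion of children with at least one recorded event depends on how often someone asks. If one arm is asked more often, its proportion rises even when the true risk is equal. An exact test of proportions takes that gap at face value.

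The visit-driven form is the problem because contact frequency is part of the treatment. Its effect depends on who fills it in. If CBT therapists do, children on CBT and on combination are asked more often than children on fluoxetine alone, and a real fluoxetine excess could be hidden. If only prescribers do, children on CBT alone have no visit forms at all, and the fluoxetine and combination arms are asked more. Ascertainment is unequal either way.

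Adverse treatment effects are among the outcomes the study aims to explore, and the community engagement section reports parents' worries about medication safety. Families and clinicians are not blinded, so nothing in the design offsets uneven asking.

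**Working it through.** **What can be reproduced.** The article gives no figure for the adverse-event comparison. The arm size used below does reproduce: 194 non-remitters / 0.60 / 0.80 = 404.2, stated as 404, or 202 per Stage 1 arm. Counting the permitted dose steps (after completed weeks 4, 6, 8, 10, 12 and 14) puts the maximum dose in study week 15, as stated.

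**Inputs for Stage 1**

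- CBT visits: 12 (stated).
- Medication visits: not stated. The fastest titration has decision points at weeks 0, 1, 4, 6, 8, 10 and 12, so 7 is assumed and other counts are tried below. A dosing rhythm is not a visit schedule.
- Fixed asks: 2 per arm (weeks 6 and 12).
- Chance of a record per ask, q: 1%, 3% or 5%, equal in both arms. These are assumptions without a source in the article.
- Test: two-sided Fisher exact at 0.05, enumerated over the two binomial distributions. The article states no alpha for adverse events.

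**Formula.** With k independent asks, P(at least one record) = 1 − (1 − q)^k.

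Pooling both sources, with therapists completing the form, k = 12 + 2 = 14 for CBT and 7 + 2 = 9 for fluoxetine. For q = 0.03 this is 1 − 0.97^14 = 34.7% against 1 − 0.97^9 = 24.0%.

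| q | CBT, 14 asks | Fluoxetine, 9 asks | False rejection, pooled | Both arms, 2 fixed asks | False rejection, fixed only |
|---|---|---|---|---|---|
| 0.01 | 13.1% | 8.6% | 25% | 2.0% | 1.7% |
| 0.03 | 34.7% | 24.0% | 62% | 5.9% | 3.0% |
| 0.05 | 51.2% | 37.0% | 80% | 9.8% | 3.4% |

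**Other medication visit counts (pooled, q from 0.01 to 0.05)**

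- 6 visits (14 v 8 asks): 37% to 94%.
- 10 visits (14 v 12 asks): 6% to 16%.
- 12 visits (14 v 14 asks): 3.6% to 4.1%, so no bias.

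**If only prescribers complete the form.** CBT alone has 2 asks and fluoxetine 9. At q = 0.03 the expected proportions are 1 − 0.97^2 = 5.9% and 24.0%. The gap is wider and runs the other way.

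**Main Effect 2.** The planned groups are about 194 / 2 = 97 each, so the same gap in proportions would reach significance less often than at 202 per arm.

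**The case against.** The strongest reply is that the article never says visit forms feed the comparison. Its adverse-event section opens with a schedule common to all arms, Table 2 shows only fixed times, and the analysis sentence gives just the coding system and the test. Choosing source and counting unit is usually left to an analysis plan, which is not shown. This stands in part: bias is a risk and not an established fact. But the article itself sends the visit forms into the study database, goes on to classify each reported event without regard to source, and contradicts Table 2 on clinician timing. An analyst following the text could reasonably pool.

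A reader might also infer that the bias runs towards CBT and so hides harm from fluoxetine. The documents do not support a direction. The CBT sections call therapists clinicians. Yet the form derives from an antidepressant questionnaire, side-effect assessment appears in the prescriber training and not in the CBT training, and the therapists' post-session reports list no side-effect form. Both readings are open.

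Three further points stand. No medication visit count is given. The independence model overstates the gap if events persist or if each report covers the time since the last one. And the illustration uses a single any-event proportion, whereas MedDRA categories would have lower rates. Adverse effects are also an exploratory aim.

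**Conclusion.** The point holds as a risk created by the text. Two sources with different exposure to asking reach one database, one unadjusted comparison of proportions follows, and the two places describing the clinician form disagree. Under the stated assumptions, with 7 medication visits, pooling gives false rejection in about 25% to 80% of trials at 202 per arm. The fixed weeks alone give about 2% to 3%. The pooled figure shrinks with closer visit counts, overlapping recall or smaller groups, and vanishes if contacts are equal.

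The documents do not show that the safety comparison will be biased, or in which direction. They leave it open to bias when an arm-neutral basis is already scheduled.

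**What to change.** - Base the between-arm adverse-event test on the child and parent forms at weeks 6, 12, 18 and 24. Count events that are new or worse than on the baseline form, which Table 2 already schedules.
- Describe clinician-visit reports separately, alongside the number of contacts in each arm, without a between-arm test.
- Keep serious adverse events from any source.
- Reconcile the adverse-event section with Table 2: state whether therapists, prescribers or both complete the clinician form, and when.

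The cost is a sentence or two in the analysis plan and one clarification in the protocol. No new data are needed, and safety monitoring at visits is unchanged. The small downside is that non-serious events seen only at clinical visits do not enter the formal test, though they are still reported.

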#### In-person and telehealth treatment

Reflecting the values of real-world implementation at the heart of PCORI’s mission, we will allow in our study the delivery of care through either in-person visits or telehealth, as routinely conducted at each of our performance sites. This modification is motivated in part by the conversion of all mental health care across our sites to telehealth to comply with safety considerations during the COVID-19 pandemic. In addition, several of our performance sites, even before the pandemic, have long histories of conducting pharmacotherapy entirely by telehealth, given the limited child psychiatry support available to cover wide geographic service regions. Moreover, the provision of psychotherapy by telehealth was accelerating at most of our sites before the pandemic. All our sites at the time of study initiation are providing all non-emergency mental health care in this medium. Following resolution of the pandemic, we anticipate that delivery of care in our study will include both telehealth and care that is delivered face-to-face. We will document for each treatment session whether it was conducted in person or via telehealth, whether the patient’s video platform was a computer or a smartphone, and whether any technical difficulties in implementation were encountered.

For patients receiving treatment via telehealth, we will assess the acceptability of telehealth treatment delivery using structured questionnaires administered to patients, parents, and clinicians after weeks 1 and 12 in Stage 1 of the study. These structured questions have been adapted from questions found in a detailed review of past studies of acceptability and feasibility for telehealth treatment delivery to either youth or adults [187–194], as well as from our initial meetings discussing telehealth experiences with patient, parent, and clinician stakeholders. We will also conduct a process evaluation using exit interviews of each of these 3 individuals (patient, parent, clinician) after week 12 using open-ended questions. This combination of structured and open-ended inquiries will provide a rich and comprehensive understanding of patient, parent, and clinician experiences with telehealth in our study.

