We will attend carefully to elements of study design and execution that enhance recruitment. Participants are often concerned about being randomized to a less effective treatment [141, 142], but here the 2 treatment arms will be in true clinical equipoise [143]. Patients will not face the possibility of being randomized to an ineffective or minimally effective treatment. This was important to the parents in our community engagement activities, who enthusiastically supported our proposed SMART design. Outcomes will be patient-centered [141], in many cases the study will be presented by their primary clinician [141, 144, 145], treatment expectations and preferences will be explored [146], informed consent will be presented simply, confidently [147], and in lay language [141, 142, 144, 145], most clinic/study visits will be scheduled after school or on weekends [144, 148], study demands will be kept to a minimum [141, 142], and patients and parents will not be blind to treatment assignment [141, 142, 145]. A large majority of participants will have Medi-Cal insurance, which does not require co-payments, so participation should not entail a financial burden [149]. We will employ the principles of QuinteT Recruitment Intervention methods, which comprise in-depth, real-time investigation of recruitment obstacles, participation, attendance, and motivation, followed by implementation of tailored strategies to address identified challenges across all treatment arms as the trial proceeds [143, 150]. We will record demographics and screening measures of all screened patients to compare those who do and do not choose to participate, to assess the representativeness of our study sample. We estimate an attrition of 20% over the 24-week RCT, yielding 323 treatment completers. If attrition proves higher, we will increase numbers recruited to ensure we achieve at least that number of completers. Our patient numbers, clinician staffing, and research coordinator burden will readily support this increased recruitment.

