(3) Group main effect ESs were then computed for a Stage 1 remission rate of 40%. Our estimated Stage 1 remission rate of 40% is a conservative estimate based on the CAMS remission rate of 35% achieved for ethnic minorities, when applying remission criteria less stringent than ours [30]. In CAMS, the 12-week remission rate was also approximately 10% higher in medication-only compared to CBT-only. We used this 10% difference in these calculations to compute ESs and resulting sample size estimates. For Main Effect 1 (start with medication vs start with CBT), ESs for all 3 medication or CBT groups (1: remitter; 2: non-remitter➔optimize monotherapy; 3: non-remitter➔medication+CBT) were computed as a weighted average of the group-specific ESs. Weights were the remission rate, with the non-remitter weight (1 minus remission-rate) split equally among the 2 randomized non-remitter groups (reflecting 1:1 Stage 2 randomization among non-remitters). For Main Effect 2 (among Stage 1 non-remitters, optimize Stage 1 treatment vs add the other treatment), ESs were computed as a weighted average of the ESs for monotherapy optimizers (medication+, CBT+) and a weighted average of the combined (medication+CBT, CBT + medication) groups. These weights were again 0.5*(1- remission-rate).

[4] We then computed the sample size required to detect Main Effect 2 (optimize monotherapy vs add the other therapy in non-remitters) at 80% power and tested at a 2-sided alpha = 0.05. From our computations above, the Main Effect 2 ES was approximately 0.40 SD, requiring a sample size of 194 participants among Stage 1 non-remitters. Increasing the sample size of 194 by the non-remission rate (N divided by non-remission rate) and by the estimated 20% dropout rate, yielded a sample size of 404 (202 per group) for Stage 1 remission rates of 40%. Randomizing 404 participants, with an estimated 324 finishing the trial and a remission rate of 40%, will provide the ability to detect an overall Main Effect 1 (medication first versus CBT first) ES of ≥0.31 SD with 80% power.

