#### Effects of treatment modality

We will evaluate the association of percentage telehealth sessions with session attendance and completion of the trial. We will also assess the influence of telehealth delivery variables (whether sessions were conducted in person or via telehealth, whether the patient’s video platform was a computer or a smartphone, and whether any technical difficulties in implementation were encountered) on treatment outcomes by including them as covariates in our sensitivity analyses.

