With an estimated 20% dropout, we will be able to detect the following effect sizes for Main Effect 1 (total *n* = 324) in various subgroups by sample representation (n): (1) Effect Size = 0.40 for 60% representation (*n* = 194); (2) Effect Size = 0.44 for 50% representation (*n* = 162); (3) Effect Size = 0.50 for 40% representation (*n* = 130). For Main Effect 2 (total n = 194), we will be able to detect: (1) Effect Size = 0.52 for 60% representation (*n* = 116); (2) Effect Size = 0.58 for 50% representation (*n* = 96); (3) Effect Size = 0.64 for 40% representation (*n* = 78). Subgroup interactions will be tested formally; with the total anticipated sample size of 324 to complete the 24-week intervention, we will have 80% power to detect subgroup differences in treatment effect sizes of ~ 0.65 and higher for Main Effect 1, and ~ 0.8 and higher for Main Effect 2.

In additional exploratory analyses, we will use latent class/profile analysis to model heterogeneity of outcome response patterns, assuming categorical latent variables (latent groups) for response. Latent class/profile analysis has been proposed as an alternative to subgroup analysis in clinical trials. As an exploratory analysis, it uses observed data (e.g., clinical characteristics, randomized treatments) to identify latent group classifications that may suggest individual characteristics related to greater responses to treatment [205].

In addition to assessing the effects of telehealth delivery of treatment on outcomes, we will assess whether the percentage of treatment sessions conducted via telehealth moderates treatment outcomes. This test will tell us whether discontinuities in telemedicine use over the course of the study or within individual patients has influenced our findings. We will also assess whether session attendance and trial completion differ by degree of participation in telehealth vs in-person intervention.

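### Relating each child's whole-course telehealth percentage to trial completion lets dropout shape the exposure, and this biases one ancillary association modestly against telehealth

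*Protocol article*

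**What the plan says.** The section In-person and telehealth treatment of the protocol article gives the starting position: "All our sites at the time of study initiation are providing all non-emergency mental health care in this medium". After the pandemic resolves, "we anticipate that delivery of care in our study will include both telehealth and care that is delivered face-to-face". It also fixes the data to be collected: "We will document for each treatment session whether it was conducted in person or via telehealth".

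Two later sections use these data for retention. Effects of treatment modality, under Sensitivity analyses, states: "We will evaluate the association of percentage telehealth sessions with session attendance and completion of the trial". HTE analysis plan restates it: "We will also assess whether session attendance and trial completion differ by degree of participation in telehealth vs in-person intervention". The latter section also plans to test whether the telehealth percentage moderates treatment outcomes, in order to learn whether "discontinuities in telemedicine use over the course of the study or within individual patients has influenced our findings". That check concerns outcomes and uses the same percentage. It is not applied to the completion analysis.

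Neither section says what the denominator of the percentage is when a course is cut short, or mentions calendar time for this analysis.

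**The concern.** The plan pairs an exposure (the percentage of a child's sessions held by telehealth) with an outcome (completion) that decides how many sessions enter the exposure. If telehealth use were constant over time, this would do no harm on average. It is not expected to be constant: care begins as all telehealth and becomes mixed. A child whose course runs across the change and who leaves early contributes mainly the earlier, telehealth-heavy sessions. A completer enrolled on the same day also contributes the later, mixed ones. The share is then partly a result of how long the child stayed, which is a form of time-dependent (immortal-time) bias.

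At stake is what the trial reports about telehealth and retention. The analysis could show lower completion with more telehealth when mode has no effect, or mask a real retention benefit.

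**Working it through.** **The plan's own figures.** The article gives no figure for the telehealth analysis, but Sample size and power and Recruitment supply the sample size and the dropout rate. From 194 non-remitters, 40% remission and 20% dropout: 194 / 0.60 / 0.80 = 404.2, against the stated 404. Completers: 404 × 0.80 = 323.2, which agrees with "We estimate an attrition of 20% over the 24-week RCT, yielding 323 treatment completers".

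**Inputs from the article.** 404 children; 20% dropout over 24 weeks; recruitment over 2 years (about 104 weeks); 12 weekly CBT sessions in each stage, so 24 weekly sessions as the model schedule.

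**Assumptions not in the article.** Entry uniform over 104 weeks; a calendar switch from 100% telehealth to a later share p of 20%, 50% or 80%; switch at week 26, 52 or 78, or gradual; dropout unrelated to mode or calendar time, with the last session L uniform on 1 to 23; sessions stop at dropout; percentage taken over sessions received.

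**Expected difference for an abrupt switch.**

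1. A course straddles the switch if the first session is before it and the 24th on or after it: 23/104 = 22% of children.
2. Let k be the number of scheduled sessions before the switch, uniform on 1 to 23 among straddlers. The fraction of a completer's sessions after the switch is (24 − k)/24, with mean (24 − 12)/24 = 0.500.
3. For a dropout with L sessions the fraction is max(0, L − k)/L. Averaged over k this is (L − 1)/46; averaged over L it is 11/46 = 0.239.
4. Dropout minus completer telehealth share among straddlers is (1 − p) × (0.500 − 0.239) = 0.261 × (1 − p). Over all children, multiply by 0.221.

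| Later telehealth share p | Straddlers (points) | All children (points) |
|---|---|---|
| 20% | 20.9 | 4.6 |
| 50% | 13.0 | 2.9 |
| 80% | 5.2 | 1.2 |

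Children treated wholly before or wholly after the switch contribute a difference of zero.

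**Simulation, no true effect of mode, 2,000 replicates per scenario, Welch t-test of share in dropouts against completers.**

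| Scenario | Difference (points) | P(p < 0.05) |
|---|---|---|
| Abrupt, week 26, 52 or 78, p = 20% to 80%, mode varying by session | 1.1 to 4.7 | 11% to 21% |
| Same, later share varying between children | 1.0 to 4.6 | 7% to 17% |
| Gradual decline over the whole study | 1.0 to 3.6 | 16% to 21% |
| Gradual, weeks 40 to 64, p = 20% or 50% | 2.9 to 4.6 | 15% to 16% |
| Abrupt, week 52, p = 50%, all dropout before week 12 | 4.3 | 22% |
| All enrolled after the switch | 0.0 | 5% |
| Every course straddles the switch, p = 50% | 13.0 | near 100% |

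The simulated differences match the closed form. With no change of mode during any course, the test holds its 5% level, so the excess comes from the change of mode and not from the test.

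**The case against.** **The shift is in calendar time.** The article describes sites moving from telehealth to mixed care across the study, not each child starting by telehealth and moving to in-person care. This stands, and it sets the size. A reader might infer that every early dropout has an inflated share and that telehealth will inevitably look harmful to retention. With everyone starting by telehealth and 3% to 12% a month moving one way to in-person care, simulation gives 4 to 13 points and 26% to 92% false positives by logistic regression. Those one-way rates are not in the article. The HTE analysis plan does allow for discontinuities within individual patients, so some within-child movement is possible, but nothing supports it as the general pattern. A child moving from in-person care to telehealth would push the bias the other way.

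**The denominator is not stated.** This also stands, and the point is conditional on sessions received. That is the natural reading, since mode is recorded for each session held. The missing-data section separates leaving the study from leaving the service as well, so some study dropouts may go on having sessions. That would weaken the effect.

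**The analysis is minor.** None of the specific aims concerns telehealth; the text says association; and exploratory analyses fall under false-discovery-rate control, so a nominal 5% test is not the planned decision rule. All of this stands and limits the consequence. It does not repair an association that the exposure's own construction partly creates.

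**Attendance.** The calculations concern dropout only, so no size is claimed for attendance.

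**Conclusion.** The point holds in a limited form. If the telehealth percentage is counted over sessions received, the completion analysis is biased towards telehealth looking worse, through children whose course overlaps a move from telehealth to mixed care. Under a calendar-time switch the pooled bias is about 1 to 5 percentage points, and the nominal 5% test rejects in about 7% to 22% of trials. These figures rest on the assumed date and shape of the switch, the assumed later telehealth share, and dropout unrelated to calendar time. They would be larger only if many children changed from telehealth to in-person care during their own course. A false finding is made more likely, not assured. Main Effects 1 and 2 and the sample size are unaffected.

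**What to change.** In Effects of treatment modality and in the matching sentence of HTE analysis plan, replace the whole-course percentage as the exposure for completion. Use a discrete-time model at session or week level, built on the per-session mode records already planned. The mode of the current session, or the share up to that point, predicts dropout before the next session, adjusted for week in study, calendar time, site and assigned treatment. The same model can serve for attendance at the next session.

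A person-week logistic model with current mode, week and week squared rejected in 3% to 7% of trials under the one-way within-child scenario with no true effect. It was not run for the calendar switch, which is one reason to include calendar time explicitly.

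Mode of the first session alone should not be relied on: it has little or no variation early in the study and is tied to calendar time.

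The cost is a change of analysis wording and a little more programming, with no new data collection.
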